### Adverse events

2.9

(Serious) Adverse Events [(S)AE] will be classified according to the Common Terminology Criteria for Adverse Events (CTCAE).

### Sample size

2.10

We calculated that 34 patients are needed to claim a successful trial with a simulated power of 84.3% under an assumed standardized effect size of 0.6 from 5,000 Monte-Carlo simulations. We used an informative Gaussian prior with a mean of 1 and a standard deviation of 1 for the expected standardized effect size. As no AHA-based effect size related to peripheral electrical stimulation was available in the literature, this prior was informed by previously reported effects in a similar population for the Jebsen–Taylor Hand Function test reporting a standardised effect size of 1.97 (9) but shifted towards a more conservative effect size. We defined a posterior probability threshold of 90% as trial success.

### Statistical analyses

2.11

The primary endpoint will be analysed using a Bayesian linear regression model with the above-specified Gaussian informative prior with mean of 1 and standard deviation of 1. We claim trial success if the probability that baseline-adjusted posterior mean difference of the primary endpoint between the groups at week 5 is greater than zero is greater than 90%. We report the posterior treatment allocation mean difference with 90% credible intervals as effect measure. Regression models are adjusted for baseline AHA and age. We perform the following sensitivity analyses. First, we use a non-informative centered Gaussian prior with variance 1,000 for the effect size. Second, because the logit-based AHA score is bounded between 0 and 100 we use Bayesian beta regression model with a logit link for the mean parameter and an identity link on the precision parameter. Because the effect estimate from a beta regression is on a log-odds scale we use a non-informative centered Gaussian distribution with variance 1,000 as prior for the effect size. We report marginal mean differences with 90% credible intervals to allow a direct comparison of the effect measure with the primary analysis.

Secondary outcomes will be descriptively reported over time (post-treatment and 12-week follow-up) and treatment group. Subgroup analyses by gender and MACS levels were *a priori* specified. We will assess the proportion of missing values only in variables, which affect the interpretation of the estimands for the primary outcome. A detailed analysis strategy (including sensitivity and subgroup analysis) has been formulated in a Statistical Analysis Plan (SAP), which was finalised before one-third of the patients were recruited. Missing data will be multiply imputed in case the proportion of missingness exceeds 5%. Otherwise, we replace missing values by the median within the corresponding treatment group. The proportion of missing values in the primary outcome at week 5 is assessed before database lock and start of the analysis. At this time point the imputation model and specification is detailed in an SAP amendment. For secondary outcomes and missing baseline variables we report complete case results.

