### Randomisation

2.6

The group allocation will follow a stratified randomization in a 1:1 ratio to ensure well-balanced division of the whole study population. The implemented stratification factors include age (6–12 years vs. 12–18 years) and the baseline measurement for the AHA, conducted at the first study visit. The randomization sequence is implemented in REDCap and generated by an independent data manager at the Clinical Trial Unit (CTU) Bern.

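### With one week-5 AHA missing, the plan fills in the arm median, ignoring the baseline AHA and age its primary model uses; the harm is small, but nothing is gained

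*Protocol article*

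**What the plan says.** All references are to the protocol article.

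Section 2.11 (Statistical analyses) sets a two-step rule. Above the threshold, "Missing data will be multiply imputed in case the proportion of missingness exceeds 5" per cent. At or below it, "Otherwise, we replace missing values by the median within the corresponding treatment group".

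The rule concerns the week-5 AHA only. The proportion that triggers it is that of the primary outcome: "The proportion of missing values in the primary outcome at week 5 is assessed before database lock and start of the analysis". Everything else is handled differently: "For secondary outcomes and missing baseline variables we report complete case results".

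The same section states of the primary model: "Regression models are adjusted for baseline AHA and age". Section 2.6 (Randomisation) makes a stratification factor of "the baseline measurement for the AHA, conducted at the first study visit", so baseline AHA should be known for every randomised child. The imputation model is left to an SAP amendment, but the median rule and the 5% switch are already fixed in the article.

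**The concern.** The primary analysis compares children at week 5 given their baseline AHA and age. The median rule gives the missing child a week-5 score that depends only on the arm. A child who started far below the rest of the arm is credited with a gain nobody observed, and a child who started far above it with a loss. The regression then reads part of that discrepancy as treatment effect. The constructed score also enters as a measured value, with no allowance for its uncertainty.

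The switch works the wrong way round. Two missing children receive a method that can use baseline information, and one missing child receives a method that cannot. Trial success rests on a single posterior probability in 34 children, so one constructed point is worth checking.

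**Working it through.** **1. When the rule applies.** N = 34 (section 2.10), allocated 1:1 (section 2.6), so 17 per arm. 5% of 34 = 1.7. One missing: 1/34 = 2.9%, median rule. Two missing: 2/34 = 5.9%, multiple imputation. The rule therefore covers exactly one missing child, taking the proportion over all randomised children.

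**2. The plan's own figure.** Section 2.10 states: "We calculated that 34 patients are needed to claim a successful trial with a simulated power of 84.3" per cent, for a standardised effect of 0.6, a N(1, 1) prior and a 90% posterior threshold. With sampling variance v = (2/17)(1 − r²) and posterior variance 1/(1 + 1/v), power is 77.0% at r = 0 and 84.3% at r = 0.52, where r is the correlation of baseline with week-5 AHA. The article does not state r. The figure has no direct bearing on the median rule; it only suggests that r near 0.5 belongs in the range examined.

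**3. Rough size by hand.** One child in an arm of 17 moves the treatment coefficient by about (filled-in value − model prediction)/17. A gap of 10, 20 or 30 AHA units gives 10/17 = 0.59, 20/17 = 1.18 or 30/17 = 1.76 units.

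**4. Simulation.** Assumed, because the article gives neither: r from 0.5 to 0.95, and an AHA SD of 20 where results are put in units. Design: 17 per arm, true difference 0, regression on arm, baseline and age, one week-5 value removed, 8,000 trials per setting. Bias and RMSE are for the regression coefficient before the prior, in SD units. False success applies the N(1, 1) prior and the 90% threshold. Each cell shows record left out / arm median.

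| Missing child | r | Bias | RMSE | False success |
|---|---|---|---|---|
| Random | 0.5 | 0 / 0 | 0.315 / 0.316 | 15.9% / 16.4% |
| Random | 0.8 | 0 / 0 | 0.217 / 0.222 | 14.4% / 14.8% |
| Random | 0.9 | 0 / 0 | 0.157 / 0.166 | 12.5% / 13.4% |
| Lowest baseline, SAES | 0.5 | 0 / +0.06 | 0.313 / 0.317 | 15.5% / 20.2% |
| Lowest baseline, SAES | 0.8 | 0 / +0.09 | 0.217 / 0.239 | 14.2% / 24.0% |
| Lowest baseline, SAES | 0.9 | 0 / +0.10 | 0.158 / 0.194 | 13.6% / 26.6% |

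A child missing at random from the lower half of the SAES arm gives a bias of about 0.025 to 0.05 SD.

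**5. In AHA units at SD 20 (separate runs).**
- Random loss: RMSE 6.23 with the record left out against 6.26 with the median at r = 0.5, and 3.06 against 3.25 at r = 0.9. The mean absolute shift between the two analyses is 0.52, 0.71 and 0.88 units at r = 0.5, 0.7 and 0.9. It exceeds 2 units in 2%, 4% and 8% of trials.
- Extreme baseline in SAES, lowest child: about +1.1 units at r = 0.5 (0.057 × 20), rising to +2.1 at r = 0.95.
- The sign reverses for the lowest-baseline control child (−1.2, −1.6, −2.0 at r = 0.5, 0.7, 0.9) and for the highest-baseline SAES child (−1.3, −1.5, −1.9).

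**6. Standard error.** At r = 0.5 with random loss, the mean SE under the median rule is 0.301 SD against a true spread of 0.316, so it is slightly too small. At r = 0.9 with the lowest-baseline SAES child missing it is 0.181 against 0.156 with the record left out, which is 16% larger (0.181/0.156 = 1.16).

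**7. Missingness that depends on the outcome itself.** At r = 0.8, if the child with the worst week-5 score in SAES is missing, both analyses are biased, the median more so (+0.107 against +0.040 SD). If it is the child with the worst baseline-adjusted result, they are about equal (+0.069 against +0.068 SD).

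**The case against.** The rule touches at most one child of 34, and the article gives no reason to expect loss to concentrate at one end of the baseline range in one arm. With a randomly lost child the average bias is zero, and near r = 0.5 the loss of precision is negligible. SD 20 and the correlations are assumptions; at SD 10 every figure in units halves. All of this stands, and it is why the point is minor.

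Several stronger readings are tempting and are not supported:
- **That the rule favours SAES.** The bias changes sign with the arm and with the end of the baseline range, so there is no built-in direction.
- **That a shift of about 2 units should be expected.** That needs a child with an extreme baseline and a high correlation.
- **That the rule always inflates the standard error.** At low correlation the standard error falls.
- **That the fault lies in using outcomes from the arm under test.** Multiple imputation by arm does that too. The fault is leaving out baseline AHA and age, and treating the value as observed.
- **That leaving the record out is always unbiased.** It is so only if missingness depends on nothing beyond baseline AHA, age and arm. When it depends on the outcome itself, both approaches are biased, and in one scenario about equally.

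What the objection does not supply is an advantage for the median. In no scenario run was its RMSE smaller than that of the analysis without the record.

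**Conclusion.** The point holds as a minor one. The article fixes a single-value rule that sets aside covariates its own primary model uses, in exactly the case of one missing child. The cost is a small loss of precision if loss is unrelated to baseline, and a bias of either sign of up to about 0.06 to 0.11 SD (1.1 to 2.1 units at SD 20) if the child's baseline is extreme. The stated standard error may be slightly too small at low correlation or inflated at high correlation.

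These sizes rest on an assumed SD of 20, assumed correlations of 0.5 to 0.95 and roughly normal scores. A reader might set the upper figure against the five-unit benchmark in section 2.7 and conclude that the primary result is in jeopardy. The article does not support that: the benchmark describes change within a child, and the upper figure is a worst case. Nor should the 77.0% above be read as an error in the stated power, since an unstated baseline adjustment would account for the difference.

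**What to change.** Delete the median rule and the 5% switch. For any missing week-5 AHA, do one of the following:
- fit the planned Bayesian model, adjusted for baseline AHA and age, to the observed week-5 outcomes; or
- multiply impute from baseline AHA, age and arm, whatever the proportion missing.

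State the assumption that missingness depends only on baseline AHA, age and arm. The SAP amendment already foreseen before database lock is the natural place to record the change.

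The cost is about one sentence. The first option needs no new code. The second needs an imputation model, which the article so far foresees only above 5% missing and has not yet specified. Neither changes the sample size, the prior or the success criterion.

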### Ethics and dissemination

2.12

The study was reviewed by the CTU in Bern and was approved by the ethics committee of the canton of Bern, Switzerland (2024-00982, accepted on the 21.05.2024, the latest Amendment 2, Version 1.3 was accepted on 11.06.2025). The manuscript includes all revisions. In case of future amendments, all relevant parties will be adequately informed.

Official monitoring by the CTU Bern was conducted over the course of the study.

Data will be securely stored using REDCap, hosted at CTU Bern. The corresponding data management file is available from the authors upon reasonable request.

The study is conducted according to the principles of the Declaration of Helsinki in its latest form.

Data privacy is ensured; each participant will receive a unique, de-identified study code, securely stored in a password-protected file.

Results will be published in peer-reviewed journals and presented at scientific meetings. Authorship will follow International Committee of Medical Journal Editors (Vancouver Convention) guidelines.

## Discussion

3

Hemiparesis is one of the leading causes of childhood disability, with a negative impact on participation and everyday life. Despite advances in therapeutic approaches, accurately assessing motor function and treatment outcomes remains challenging in young populations during development. SAES has been proven effective in adult populations. Due to developmental differences in children and adults, it is crucial to study the effect of SAES in the paediatric population independently of the adult population.

This study will examine the efficacy of SAES to improve UL motor and sensory function and activity in everyday life. We will use innovative, novel methods to assess bimanual hand functions and a multimodal research approach to disentangle the neuroplastic mechanisms underlying SAES. Our primary outcome, the AHA, was selected due to its clinical relevance and because it reflects spontaneous use of the affected hand in bimanual activities, which is highly relevant to everyday functioning. Secondary endpoints assess motor and sensory functions to explore potential mechanisms of action and determine whether improved hand use is linked to changes in motor control and sensorimotor integration, offering further insight into clinical outcomes. Our study focuses on treatment optimization, as our findings will give insights into how SAES impacts hand functions and cerebral sensorimotor networks in a comparably large patient cohort. Hence, the present study has high clinical implications and will contribute to the enhancement of new diagnostic treatment strategies.

## Limitations

4

This study design has several limitations we would like to acknowledge. Firstly, the relatively small sample size of 17 children per study arm was calculated having the primary outcome in mind, which poses considerable limitations on the statistical power of our secondary outcomes. This limitation is most pronounced for the MRI and TMS outcomes, since these two assessments impose additional exclusion criteria further reducing the number of participants. A second limitation concerns the sample size calculation itself. As no AHA-based effect sizes were available from prior sensory afferent electrical stimulation trials in this population, the informative prior was derived from an effect size for a different outcome measure in a related electrostimulation trial (9). While this effect size was scaled down conservatively, this introduces uncertainty into the sample size and power calculation.

A third limitation concerns the missing blinding of participants and their families, which is not feasible in the design of this intervention trial. Since participants are aware whether or not they are receiving the stimulation, this could potentially bias our outcome measures. This is especially true for our subjective outcomes such as the KidScreen or the COPM.
